## Abstract

**Background:**

Between 25% and 30% of patients hospitalised for acute heart failure (AHF) are readmitted within 90 days after discharge, mostly due to persistent congestion on discharge. However, as the optimal evaluation of decongestion is not clearly defined, it is necessary to implement new tools to identify subclinical congestion to guide treatment.

**Objective:**

To evaluate if inferior vena cava (IVC) and lung ultrasound (CAVAL US)-guided therapy for AHF patients reduces subclinical congestion at discharge.

**Methods:**

CAVAL US-AHF is a single-centre, single-blind randomised controlled trial designed to evaluate if an IVC and lung ultrasound-guided healthcare strategy is superior to standard care to reduce subclinical congestion at discharge. Fifty-eight patients with AHF will be randomised using a block randomisation programme that will assign to either lung and IVC ultrasound-guided decongestion therapy (‘intervention group’) or clinical-guided decongestion therapy (‘control group’), using a quantitative protocol and will be classified in three groups according to the level of congestion observed: none or mild, moderate or severe. The treating physicians will know the result of the test and the subsequent adjustment of treatment in response to those findings guided by a customised therapeutic algorithm. The primary endpoint is the presence of more than five B-lines and/or an increase in the diameter of the IVC, with and without collapsibility. The secondary endpoints are the composite of readmission for HF, unplanned visit for worsening HF or death at 90 days, variation of pro-B-type natriuretic peptide at discharge, length of hospital stay and diuretic dose at 90 days. Analyses will be conducted as between-group by intention to treat.

**Ethics and dissemination:**

Ethical approval was obtained from the Institutional Review Board and registered in the PRIISA.BA platform of the Ministry of Health of the City of Buenos Aires.

**Trial registration number:**

NCT04549701.

WHAT IS ALREADY KNOWN ON THIS TOPICRemaining clinical congestion at discharge is a strong predictor of mortality and readmissions in patients hospitalised for acute heart failure (AHF). However, the optimal assessment of decongestion and how to guide treatment are not clearly defined.WHAT THIS STUDY ADDSThe inferior vena CAVA and Lung UltraSound-guided therapy in Acute Heart Failure (CAVAL US-AHF) is a single-centre, single-blind randomised controlled trial. It will provide evidence on the usefulness of this innovative ultrasound protocol that evaluates both right-sided congestion through the evaluation of the inferior vena cava and left-sided congestion through lung ultrasound to guide pulmonary decongestion in patients hospitalised for AHF.HOW THIS STUDY MIGHT AFFECT RESEARCH, PRACTICE OR POLICYCAVAL US-AHF could provide evidence on the use of a simple, non-invasive technique to guide treatment during hospitalisation for AHF with the goal of achieving clinical and subclinical decongestion to potentially decrease the risk of events after discharge.

## Introduction

Despite the important therapeutic advances, the prevalence of heart failure (HF) is increasing^1^ and is still a major healthcare issue due to its high morbidity and mortality.^2^ Approximately 25%–30% of patients hospitalised for acute HF (AHF) are readmitted within 90 days after discharge, and 50% within 6 months.^3–5^ The post-discharge period, known as the ‘vulnerable phase’,^6^ is associated with high risk of unfavourable outcomes.^7 8^ Readmission of these patients does not only increase costs but is also a signal that current approaches to HF management are not optimal. In fact, the greatest threat to patients with AHF is the risk of readmission due to persistent congestion.^9–11^

Remaining clinical congestion at discharge is a strong predictor of mortality risk^12 13^; therefore, its assessment prior to hospital discharge remains a crucial opportunity to treat patients who have not yet reached the optimal euvolemia. However, the optimal evaluation of decongestion in AHF is not clearly defined in the guidelines,^14 15^ which may be partly explained by the lack of effective measurement methods.^10 16^ Monitoring patient fluid status is a dynamic and challenging process with a broad spectrum of clinical presentations and parameters to consider. Physicians are faced with the daily task of making critical decisions with a handful of tools and a significant gap in evidence as above mentioned.^17^

Evaluation and monitoring of fluid excess status in patients admitted for acute decompensated HF are currently based on clinical history, physical examination, chest X-ray and natriuretic peptides.^10^ However, all these elements have an inherent substantial interobserver variability and may be non-specific,^18 19^ and plasma levels of biomarkers have a limited capacity to assess quantitatively the extent of fluid retention.^20^

Lung ultrasound (LUS) has been introduced in the evaluation of pulmonary congestion.^21^ The number of B-lines is a reliable marker of the presence of extravascular lung water and has allowed the identification of patients with HF with worse prognosis. Several publications have demonstrated the usefulness of B-lines in the outpatient follow-up of patients with chronic HF to reduce the number of hospitalisation rates due to AHF.^22–24^ In patients hospitalised for AHF, residual pulmonary congestion assessed by LUS was a strong predictor of short-term mortality and rehospitalisation.^25–28^ Recently, a study analysed the prognostic capacity of the presence of B-lines in patients in whom their treating physicians considered them properly lung decongested. Up to 40% of patients, considered decongested according to pulmonary auscultation, present subclinical congestion at hospital discharge which implies a worse prognosis at 6-month follow-up.^28^ This congestion can be detected by LUS.

Measurement of the inferior vena cava (IVC) diameter by ultrasound is a simple method to estimate right atrial pressure and is associated with changes in pulmonary capillary pressure.^29^ Increased diameter and collapsibility of the IVC in the outpatient setting predict a higher risk of hospitalisation and mortality due to AHF.^30 31^ In patients hospitalised for AHF, therapy guided by IVC diameter is associated with a reduction in 30-day readmission^32^ and mortality rates.^33^

In a small recent pilot study, a protocol combining focused echocardiographic evaluation of cardiac filling pressures, and IVC index with LUS resulted safe and reliable for guiding treatment in hospitalised patients with AHF.^34^

To date, no randomised trials have investigated the usefulness of the evaluation of right-sided congestion through the IVC and left-sided congestion through LUS to guide therapy in hospitalised patients with AHF, with the aim of improving the decongestion at discharge.

Inferior vena CAVA and Lung UltraSound-guided therapy for the reduction of clinical events in Acute Heart Failure (CAVAL US-AHF) pilot trial has been designed to evaluate if IVC and LUS-guided therapy is superior to standard care to reduce subclinical congestion at discharge, and secondarily, to explore whether it reduces clinical events at 90 days. This report describes the rationale and study design of this trial.

## Methods

We designed a single-centre, single-blinded, randomised controlled clinical trial (NCT04549701). The flow diagram of the trial is shown in figure 1.

**Figure 1 F1:**
[figure not shown]
Trial diagram. AHF, acute HF; CAVAL US, inferior vena cava and lung ultrasound; HF, heart failure.

### Participants and eligibility

Patients admitted with AHF in a private cardiovascular centre in Buenos Aires, Argentina. Eligibility criteria for participants are described in box 1.

Box 1Eligibility criteriaInclusion criteria (all of them)Hospitalisation of 24 hours or more for decompensated heart failure (HF) defined as new onset of symptoms or worsening of previous symptoms (including orthopnoea, progression to functional class New York Heart Association III–IV, bendopnoea or fatigue) or signs of volume overload.Jugular venous distension, hepatojugular reflux, lower extremity oedema or signs of pulmonary congestion.Chest X-ray with signs suggestive of pulmonary congestion.Elevated pro-B-type natriuretic peptide levels of 450 pg/mL, 900 pg/mL and 1800 pg/mL for ages <50 years, 50–75 years and >75 years, respectively, within 24 hours of admission.^53^
^54^
Sufficient ultrasound visualisation to assess inferior vena cava and lungs.Exclusion criteria (any of them)Not willing to participate.Life expectancy of less than 6 months.Uninterpretable lung or inferior vena cava ultrasound.Transfer to another hospital before hospital discharge.Systolic blood pressure <90 mm Hg.Chronic kidney disease (creatinine clearance <30 mL/min calculated with the Modification of Diet in Renal Disease (MDRD) study equation or haemodialysis).Requirement for invasive or non-invasive ventilator support.Pregnancy.Low cardiac output syndrome/cardiogenic shock.Death during index hospitalisation.Acute coronary syndrome, myocardial revascularisation or heart valve replacement within the previous 3 months.Being on heart transplant waiting list.Cardiac resynchronisation therapy device implanted within the previous 3 months.Severe tricuspid valve regurgitation.HF secondary to causes amenable to invasive correction: cardiac surgery, percutaneous interventions or pacemaker implantation.HF secondary to significant arrhythmias (advanced atrioventricular block or sinus arrest, sustained ventricular tachycardia or any sustained arrhythmia other than atrial fibrillation causing haemodynamic instability according to the discretion of the treating physician).HF secondary to severe systemic infection.Severe psychiatric illness.Palliative care.SARS-CoV-2 infection.

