### Randomisation

Patients will be randomised using a block randomisation programme that will assign to either lung and IVC ultrasound-guided decongestion therapy (‘intervention group’) or clinical-guided decongestion therapy (‘control group’). Randomisation will be stratified by age (<70 or >70 years) and by left ventricular function (<50% or >50%). Randomisation will be performed within 24 hours after hospital admission using the REDCap randomisation module with a 1:1 allocation scheme.

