### Study endpoints and follow-up

The primary endpoint is the presence of subclinical congestion at discharge, defined as the presence of more than five B-lines and/or an increase in the diameter of the IVC, with and without collapsibility.

The secondary endpoint is the composite of readmission for HF, unplanned visit for worsening HF or death at 90 days. Additionally, we will assess other secondary endpoints such as the variation of pro-B-type natriuretic peptide at discharge, length of hospital stay, total number of HF hospital admissions and diuretic dose at 90 days (box 3). AHF hospitalisation was defined as unscheduled urgent hospital visit and hospital stay >24 hours, requiring intravenous HF therapies (diuretics, vasodilators, inotropes). Urgent AHF visits were defined as unscheduled visit to the emergency department resulting in increased dose of oral/intravenous therapy, stay <24 hours.

Box 3Secondary endpointsComposite outcome: readmission for heart failure (HF), unplanned visit for worsening HF or death at 90 days.All-cause mortality at 90 days.Duration of index hospital stay.Reduced total readmissions (first and recurrent) for HF at 90 days.Increased requirement for diuretics: patients who required a higher dose of furosemide compared with the dose indicated on hospital discharge.Pro-B-type natriuretic peptide (NT-proBNP) at discharge.% change of NT-proBNP (admission–discharge).

The safety endpoints during the index hospitalisation include:

Hypotension (systolic blood pressure <90 mm Hg).Requirement of vasoactive drugs (inotropic/pressor agents).Worsening renal function leading to a creatinine increase of ≥50% or >0.3 mg/dL on any of the blood tests performed during the index hospitalisation.Hypokalaemia <3.5 mmol/L or hyperkalaemia >5 mmol/L.

At 90 days after randomisation, two independent physicians, blinded to the assigned group, will adjudicate events by telephone contact. In case of disagreement, a third independent physician will evaluate the case.

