### Statistical analysis plan

According to our preliminary pilot data derived from a sample of 20 patients during the new ultrasound tool proof trial, 70% had >5 B-lines and/or dilated IVC at discharge with the usual care strategy at our hospital. Therefore, to reach a relative risk reduction of 50% (ie, 70% in usual care and 35% in the CAVAL US-guided strategy), setting a power of 80% and a two-sided type I error rate of 5%, we will need 29 patients in each arm to accomplish our hypothesis.

Analysis will be performed by intention to treat. Continuous variables will be expressed as mean and SD, or median and IQR, according to their distribution. Normality of distribution of variables will be assessed using the Kolmogorov-Smirnov test or the Shapiro-Wilk test, according to the sample size. Continuous variables will be compared using the Student’s t-test or the Mann-Whitney U test, as applicable. Categorical variables will be presented as numbers and percentages. The Χ^2^ test or Fisher’s exact test will be used to compare proportions. No imputation will be made for missing data.

The Kaplan-Meier method will be used to analyse time-to-first event data. The differences in time-to-event distributions will be evaluated using the log-rank test. Univariate HRs with associated 95% CIs will be estimated for the composite primary endpoint and secondary endpoints and derived from the Cox proportional-hazards model; however, multivariate Cox regression analysis will only be used if there are important prognostic factors or patients’ baseline characteristics exhibiting significant imbalance between the two groups established by randomisation. In all cases, the alpha error will be set at 5% to establish statistical significance. All the statistical calculations will be performed using SPSS V.24 software package.

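### In-hospital death and transfer are listed as exclusion criteria although both can only happen after randomisation, which contradicts the intention-to-treat analysis

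*Protocol article*

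**What the plan says.** - **Eligibility (Participants and eligibility, Box 1).** Any single exclusion criterion is enough to exclude. The list includes "Death during index hospitalisation" and "Transfer to another hospital before hospital discharge". The inclusion list also asks for a hospital stay of at least 24 hours.
- **Timing (Randomisation).** "Randomisation will be performed within 24 hours after hospital admission".
- **Analysis (Statistical analysis plan).** "Analysis will be performed by intention to treat", and "No imputation will be made for missing data". The abstract also names intention to treat.
- **Endpoints (Study endpoints and follow-up, Box 3).** "The primary endpoint is the presence of subclinical congestion at discharge". Secondary endpoints include all-cause mortality at 90 days and a composite that contains death. Events are adjudicated at 90 days counted from randomisation. The safety endpoints (hypotension, vasoactive drugs, worsening renal function, potassium disturbance) are collected during the index stay.

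The article does not say how a randomised patient who dies or is transferred before discharge is analysed.

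**The concern.** An eligibility rule should use only what is known when the patient is randomised. In-hospital death and transfer are later events. Most other Box 1 exclusions, such as blood pressure, renal function, ventilatory support and shock, can be read as the patient's state at entry. These two cannot.

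The strategy under test changes decongestion treatment during the stay, so it can influence who dies or is transferred. Removing patients for those events selects on something that follows allocation, and the removal may differ between arms. If the ultrasound-guided strategy caused harm in hospital, the patients who showed it would be the ones taken out. The 90-day mortality endpoint and the composite would lose deaths that fall within 90 days of randomisation. The safety endpoints would lose patients who plausibly had safety events before they died.

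**Working it through.** **1. The passages side by side**

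| Item | When it can be known | Consequence if applied |
|---|---|---|
| Randomisation | Within 24 h of admission | Fixes the intention-to-treat set |
| Death during the index stay | After randomisation | Removes a randomised patient |
| Transfer before discharge | After randomisation | Removes a randomised patient |
| 90-day mortality and composite | Adjudicated 90 days after randomisation | The period includes the index stay, so in-hospital deaths belong in it |
| Safety endpoints | During the index stay | Patients who die in hospital belong in them |

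Box 1 as written and analysis of all randomised patients cannot both hold.

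**2. The plan's own sample size**

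Inputs from the Statistical analysis plan: 70% v 35%, 80% power, two-sided 5%. With unpooled variance,

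n = (1.96 + 0.84)² × (0.70×0.30 + 0.35×0.65) / 0.35² = 7.849 × 0.4375 / 0.1225 = 28.03, rounded up to 29 per arm.

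This matches the article. The pooled-variance formula gives 31, and its power at 29 per arm is 77.5%.

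**3. Effect on the primary comparison (illustration)**

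The planned rates in 29 per arm are about 10/29 (0.35 × 29 = 10.15) and 20/29 (0.70 × 29 = 20.3) with subclinical congestion. For a table with a, b in one arm and c, d in the other, the uncorrected chi-square is N(ad − bc)² divided by the product of the four margins.

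- Planned effect, no deaths, 10/29 v 20/29: 58 × 290² / (29×29×30×28) = 6.905, p = 0.0086.
- Three deaths, all in the intervention arm and all otherwise free of the endpoint:
  - excluded, 10/26 v 20/29: 55 × 230² / (26×29×30×25) = 5.145, p = 0.023
  - counted as failures, 13/29 v 20/29: 58 × 203² / (29×29×33×25) = 3.445, p = 0.063
- Two deaths under the same assumptions: 10/27 v 20/29 gives p = 0.017; 12/29 v 20/29 gives p = 0.035. With Fisher's exact test, which the plan also allows, these become 0.031 and 0.064.
- One death in each arm, both otherwise free of the endpoint:
  - excluded, 10/28 v 20/28: 56 × 280² / (28×28×30×26) = 7.179, p = 0.0074
  - counted as failures, 11/29 v 21/29: 58 × 290² / (29×29×32×26) = 6.971, p = 0.0083
- Three intervention-arm deaths among patients who already had the endpoint: excluded, 7/26 v 20/29, p = 0.0018; counted, 10/29 v 20/29, p = 0.0086.

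**4. Effect on numbers**

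The article gives no rate of in-hospital death or transfer. Assuming 2% to 10% of randomised patients are removed (about 1 to 6 of 58), the number evaluable per arm falls from 29 to between 28.4 and 26.1. Pooled-formula power falls from 77.5% to between 76.7% and 72.9%. The loss of power is small; the issue is bias.

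**5. Effect on mortality**

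Two in-hospital deaths in an arm of 29 (2/29 = 6.9%) would be reported as none if Box 1 were applied.

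**The case against.** The case on the other side has real weight on scope and size.

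- **Intention to treat is not ruled out.** A reader might infer that the analysis cannot be done. The Statistical analysis plan section nowhere says randomised patients will be removed, and if it takes precedence over Box 1 the analysis is feasible. The flow diagram, which might show where exclusions operate, is not available here. This objection stands: the documents support a contradiction to be reconciled, not an impossibility.
- **The 24-hour stay is not a third example.** A reader might count it as one. It is an inclusion item, it can mean expected stay, and the endpoint section uses the same threshold to separate a hospitalisation from an urgent visit. It needs only clarification.
- **The 90-day clock is not fully explicit.** Ninety days after randomisation is stated as the time of adjudication, and readmission presupposes discharge. This weakens the point somewhat for the composite and hardly at all for all-cause mortality. No clock starting at discharge is set for either endpoint.
- **The adverse p-values are a worst case.** They place every death in one arm and treat each of those patients as otherwise a success. Three of 29 is about 10%, in a population that excludes shock, low blood pressure and ventilatory support. This stands, and it limits what the figures show.
- **The missing-data rule adds little.** An endpoint measured at discharge is undefined for someone who dies first, whatever the imputation policy. This also stands.

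None of these gives in-hospital death or transfer a meaning at baseline, so the core conflict remains.

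**Conclusion.** The point holds for two Box 1 items, in-hospital death and transfer. As written they exclude patients after randomisation for events that the allocated strategy may influence, against the plan's own analysis population. If Box 1 is applied, in-hospital deaths are lost from 90-day all-cause mortality, the composite and the safety endpoints.

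The size cannot be fixed from the article. A reader might infer from the worst case that the exclusions would decide the trial. The documents do not support that: the shift across 5% depends on assumed numbers of deaths, all in the intervention arm and all otherwise successes, while one death per arm leaves the result essentially unchanged. The defect does not depend on these figures.

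**What to change.** 1. Delete in-hospital death and transfer from the exclusion criteria, so that eligibility uses only facts known at randomisation.
2. Define the analysis set as all randomised patients, analysed as allocated.
3. Count in-hospital deaths in 90-day mortality, the composite and safety.
4. Report pre-discharge deaths and transfers by arm.
5. Prespecify how these patients enter the discharge endpoint. Counting death before discharge as failure, with a complete-case sensitivity analysis, is one defensible choice. It changes the target of estimation to a composite, which should be said openly. For transfers, using the last earlier scan would conflict with the no-imputation rule and would assume a scan schedule that the article does not give, so any such rule must be reconciled with both.
6. Clarify that the 24-hour stay item describes the expected admission and is not a ground for removing randomised patients.

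The cost is a protocol wording change and a little extra analysis and reporting. It needs no additional patients.

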### Randomisation

Patients will be randomised using a block randomisation programme that will assign to either lung and IVC ultrasound-guided decongestion therapy (‘intervention group’) or clinical-guided decongestion therapy (‘control group’). Randomisation will be stratified by age (<70 or >70 years) and by left ventricular function (<50% or >50%). Randomisation will be performed within 24 hours after hospital admission using the REDCap randomisation module with a 1:1 allocation scheme.

### Study intervention

Our hospital practice is based on clinical guidelines,^15^ and all the patients admitted for HF will be evaluated and treated by the same medical team, composed of physicians specialised in cardiovascular diseases.

The diuretic treatment algorithms proposed by the Heart Failure Association of the European Society of Cardiology^35^ and the American College of Cardiology^36^ were adapted, and the CAVAL US protocol was added as part of the daily assessment of congestion (figure 2).

**Figure 2 F2:**
[figure not shown]
Therapeutic algorithm. Adapted from: Mullens *et al*
35 and Hollenberg *et al*.^36^ BP, blood pressure; CAVAL US, inferior vena cava and lung ultrasound; IV, intravenous; LCOS, low cardiac output syndrome; UO, urinary output.

All the patients will undergo lung and IVC ultrasound, independently of the group assigned during randomisation. Furthermore, an echocardiogram will be performed within 48 hours from admission according to the recommendations,^15^ as part of our standard of care.

A checklist will be made prior to hospital discharge to assess compliance with guideline-based treatment, vaccination, counselling and medical appointment after discharge. All patients will receive education by an HF nurse, who will provide educational material and drug treatment indications in a written grid.

Patients will be randomised into two arms and will be blinded to the assigned arm:

Control group: the treating medical team will be blinded to the lung and IVC ultrasound results. Patients will receive the standard of care of our centre and titration of diuretics will be based on standard practices (physical examination, symptoms and results of laboratory tests). The therapeutic goal (see figure 2) will be to discharge patients with relief of signs and symptoms of congestive HF, without ECG changes or abnormal laboratory findings that contraindicate hospital discharge. Circulating biomarkers of congestion are not part of the standard of care.Intervention group: the treating medical team will be unblinded to the lung and IVC ultrasound results. Patients will receive treatment for decongestion according to the results of the intervention plus the standard care (figure 2). The therapeutic objectives will be similar to the control group, with relief of the signs and symptoms of HF and additionally without congestion or mild residual congestion in the ultrasound test. At the discretion of the treating physician, the patient may be discharged when he or she shows mild to moderate signs of congestion in improvement with oral diuretics for more than 24 hours with adequate diuretic response.

Both groups will be scheduled to follow-up visits in our ambulatory clinic 7–10 days after discharge, and at least once per month.

